**MHELW training/recruitment**

We will seek to recruit individual with a minimum of 6 months experience of providing mental health and wellbeing services and have experience in providing advice, information and support about workplace wellbeing and positive mental health at work. MHELW will be trained (jointly with research team members) and employed by the charity Mind (or local Minds), who have taken leadership in defining and developing the role via their established service design and development process. A training programme will be developed and delivered to the MHELWs as a coherent group, so that individuals can learn together and the group can test out ideas, define the boundaries of the intervention and further develop it. The training will take place over the course of two weeks. Subsequent to the training, there will be ongoing joint supervision of the MHELW via meetings held at least monthly, as well as a ‘buddy system’ for peer support. The MHELWs will also have line managers for support within local Minds. Aspects that the manual and training will cover includes (but not limited to):

1. What MHELW can or cannot do
2. Very strong role of consent
3. Adherence to medication
4. Interaction with legal framework
5. Competencies
6. Minimum and maximum number of sessions

**Control group**

Participants eligible for this intervention who are not randomised to the intervention arm, will be entered into a waiting list control arm. The control arm will receive the same intervention after a 3-month delay.

**Randomisation**

Individuals will be randomised to the intervention and the control group. Although stratification at the organisational level by size (large, medium, or small) and location (LEPs) is not practical in this study, these organisational characteristics along with demographic (age, gender, SES) and work environment characteristics (industry, job nature) will be included in our exploratory analyses as covariates. Randomisation will be carried out via a computer-generated random allocation sequence by a researcher independent to the study.

**Full** **randomised controlled trial sample size**

There have been no previous randomised controlled trial (RCT) studies reporting effect sizes of liaison workers intervention programmes on work productivity. With limited empirical findings to base our sample size calculations on, we estimate a small to medium effect size of (d=0.33). The estimated sample size necessary to detect an effect size (Cohen’s d) of 0.33 at an alpha error rate of 0.05 (two-tailed) and a beta error rate of 0.20 using the G* Power 3 program was 292 participants (146 participants per arm) [17-18]. However, we anticipate we may need to obtain consent from up to 365 participants at randomisation, anticipating a 25% attrition rate. This equates to a N point difference between the arms in our primary outcome measure.

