**Feasibility randomised controlled trial sample size**

There are currently no clear guidelines for estimating an appropriate sample size for feasibility studies. This is not a hypothesis testing study and therefore the sample size is based on pragmatic assumptions around feasible recruitment figures and the number of participants required to estimate the key parameters around the feasibility of a full RCT based on the sample size calculation. As per standard practice in feasibility RCTs, no formal power calculation is required [14]. A recommended sample size between 24 [19] and 50 [20] participants per arm for feasibility RCTs will be used, consistent with the median sample size found in pilot RCTs [21]. We aim to recruit 56 participants (15% of the full RCT sample size) to the whole study, who will be randomised into either the intervention or the waitlist control group (28 participants per arm) factoring a 25% attrition rate as describe above for the full RCT.

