***Feasibility and acceptability of MHELW intervention (measured at 3 months).***

**Feasibility:**

- Recruitment of 15% (n=55) employees of the full RCT sample size (n=365 with 25% attrition rate) in a 5-month recruitment period (May to end of September 2021)
- Retention rate of ≥60% as measured by attendance at the post intervention assessment
- Estimates of eligible participants recruited, failures to recruit due to recruitment issues and participants dropping out due to feasibility issues
- Completion rate of study questionnaires (employee and line manager) at baseline and 3 months for both intervention and control groups, reported as percentage missing data for each assessment schedule at baseline and 3 months.

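### The full-RCT figure of 365 allows for 20% attrition, not the stated 25%; the consistent figure is 390, and the 15% tied to it needs restating

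*Protocol*

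**What the plan says.** Under Full randomised controlled trial sample size, the protocol assumes a standardised difference of 0.33, a two-tailed alpha of 0.05 and "a beta error rate of 0.20 using the G* Power 3 program". It reports that the required number "was 292 participants (146 participants per arm"). It then allows for loss to follow-up: "we anticipate we may need to obtain consent from up to 365 participants at randomisation, anticipating a 25% attrition rate". The paragraph ends: "This equates to a N point difference between the arms in our primary outcome measure".

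The figure is used again in the first criterion under Feasibility: "Recruitment of 15% (n=55) employees of the full RCT sample size (n=365 with 25% attrition rate"), to be reached in a five-month recruitment window.

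Feasibility randomised controlled trial sample size gives a slightly different number for the same target: "We aim to recruit 56 participants (15% of the full RCT sample size) to the whole study", that is, 28 per arm. That section also says that the size is pragmatic, that no formal power calculation is needed, and that 24 to 50 per arm is the recommended range.

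**The concern.** An attrition rate is a share of those randomised. To keep 292 after losing 25%, one divides 292 by 0.75. The protocol's figure matches multiplication by 1.25 instead, which adds a quarter of the completers rather than allowing for the loss of a quarter of those randomised. The stated attrition and the stated number at randomisation therefore do not agree.

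Two things are at stake. The figure of 365 is the headline number that this feasibility study hands to the definitive trial, and at the protocol's own attrition rate it falls short of the stated power. It is also the denominator of the recruitment criterion, so the 15% quoted there and in the feasibility sample-size section refers to a total that does not follow from its inputs.

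The unfilled "This equates to a N point difference between the arms in our primary outcome measure" is a separate, smaller defect. It neither causes the inflation error nor adds weight to it, but it means that 0.33 is never translated into points on the Work Productivity and Activity Impairment scale (WPAI).

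**Working it through.** **Inputs, all from the protocol:** d = 0.33; alpha = 0.05 two-sided; power = 0.80; 1:1 allocation; 292 analysable; 25% attrition; 365 at randomisation; recruitment targets of 56 and 55.

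**1. Reproduce the analysable number.** The normal approximation gives 145 per arm (290). The two-sample t-test gives 145.1 per arm, rounded up to 146, so 292. Power at 146 per arm is 80.2%. The 292 is right and contains no allowance for attrition.

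**2. Reproduce the number at randomisation.**
- Multiplying: 292 × (1 + 0.25) = 365. This matches the protocol exactly.
- Dividing: 292 / (1 − 0.25) = 389.3, rounded up to 390 (195 per arm).
- Attrition that 365 actually covers: 1 − 292/365 = 0.20.
- Shortfall: 390 − 365 = 25, and 25/390 = 6.4%.

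**3. Power at 25% attrition (two-sample t-test, d = 0.33).**

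| Randomised | Completers | Per arm | Power |
|---|---|---|---|
| 365 | 365 × 0.75 = 273.75 | 136.9 | 77.6% (77.7% at 137 per arm) |
| 390 | 390 × 0.75 = 292.5 | 146.25 | 80.3% |

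The normal approximation gives 77.9% and 80.6%. With 365 randomised there are about 18 fewer completers than the 292 required (292 − 274). At that size, 80% power is reached at d = 0.34 rather than 0.33.

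**4. Carry-through to the recruitment target.**
- 15% of 365 = 54.75, the source of the 55. 56/365 = 15.3%.
- 15% of 390 = 58.5. 56/390 = 14.4%. 55/390 = 14.1%.

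If 365 alone were replaced under Feasibility, the criterion would then label 55 as 15% of 390, which it is not. The percentage has to change with it. The step from 55 to 56 may be rounding to equal arms, but the protocol does not say so.

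**5. The placeholder.** The target difference in points is 0.33 × SD. The protocol gives no SD for any WPAI metric. For an assumed SD of 20 points it is 0.33 × 20 = 6.6; for an assumed SD of 30 it is 0.33 × 30 = 9.9. These values show scale only.

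**The case against.** The best case for leaving the text alone is that 365 is a provisional figure for a trial not yet designed, and the protocol hedges it. No one in the present study is recruited, randomised or analysed differently because of it. The loss is a little over two points of power, the same as moving d from 0.33 to 0.34, and the protocol admits that there is little evidence behind 0.33. The 25% is provisional too: the retention criterion accepts 60%, at which 292/0.60 = 486.7, so 487, would have to be randomised. Retention is one of the things this study measures, so the full-RCT number will probably be recalculated.

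All of that stands, and it limits the severity. It does not make the figure right. Even as an upper limit, 365 is below the 390 that the protocol's own inputs require, and the figure is repeated with the 25% beside it under Feasibility.

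A reader might go further and infer that the feasibility target is itself wrong, or that this study must recruit about 59. The documents do not support that. The feasibility size is justified on pragmatic grounds without a power calculation, and 28 recruited per arm lies within the range of 24 to 50 that the protocol cites. The 15% is a chosen fraction; nothing in the protocol makes 15% of 390 a more valid test of recruitment than 55 or 56.

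**Conclusion.** The point holds as an arithmetic inconsistency. The number at randomisation for the full RCT corresponds to 20% attrition, while the text states 25%. At 25% the consistent number is 390; 365 is 25 short (6.4%) and gives about 77.7% power instead of 80%. This rests on the protocol's own effect size, alpha, power and attrition, on a two-sample t-test, and on attrition meaning a share of those randomised.

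The feasibility sample of 56 is not invalidated. Only its description as 15% of the full RCT changes, to about 14%, and the two recruitment numbers of 56 and 55 need to be made the same. The blank target difference is a separate minor omission. Taken together, the severity is minor to moderate.

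**What to change.** 1. Under Full randomised controlled trial sample size and under Feasibility, replace 365 with 390 (195 per arm), and show the calculation as 292 / 0.75.
2. Keep the feasibility size at 56 (28 per arm), and use the same recruitment number in the feasibility sample-size section and in the recruitment criterion.
3. In both of those places, restate the 15% as about 14% of the full RCT (56/390 = 14.4%), or drop the percentage and leave the absolute target.
4. Complete the sentence on the target difference as 0.33 × SD, with the SD stated as an assumption. Intended primary outcome: work productivity lists absenteeism, presenteeism and overall impairment without choosing one, so the sponsor should first name the metric to which the difference applies.

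The cost is a correction of numbers and wording. The projected size of the future trial rises by 25; no participant is added to this study, and its conduct does not change.

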**Feasibility randomised controlled trial sample size**

There are currently no clear guidelines for estimating an appropriate sample size for feasibility studies. This is not a hypothesis testing study and therefore the sample size is based on pragmatic assumptions around feasible recruitment figures and the number of participants required to estimate the key parameters around the feasibility of a full RCT based on the sample size calculation. As per standard practice in feasibility RCTs, no formal power calculation is required [14]. A recommended sample size between 24 [19] and 50 [20] participants per arm for feasibility RCTs will be used, consistent with the median sample size found in pilot RCTs [21]. We aim to recruit 56 participants (15% of the full RCT sample size) to the whole study, who will be randomised into either the intervention or the waitlist control group (28 participants per arm) factoring a 25% attrition rate as describe above for the full RCT.

**Recruitment**

**Expression of interest employee**

Awareness of the Mental Health Productivity Pilot (MHPP) programme will have been raised within organisations (via initiatives such as the Thrive Plus programme) and expression of interest though the Mental Health Productivity Pilot website (<https://mhpp.me/>). We will recruit businesses to be part of the study through the network that we have already established during proposal scoping and the earlier studies. They will all be given the opportunity to take part subject to local service delivery partner availability. We have already received expressions

of interest from widely different businesses. Businesses will be asked to advertise the study to potential participants (employee and line managers) via emails, direct communications, signs in communal staff areas such as break rooms or canteens, staff bulletins and newsletters. Once partners have signed up, we will gather interest from employees who wish to take part in the study and screen them to identify eligibility. We will also be advertising the study directly to employees in the wider Midlands community.

**Direct recruitment of employees and line managers**

The study will be advertised to the wider working community, who are not employees of partners, using a variety of local and online recruitment strategies. Advertising and recruitment materials for individuals are additional to the materials used for recruiting employees through employers. All advertising materials for individual recruitment include a link to a mirroring version of the study website, intended for these employees

Advertising to individuals may include:

- Advertisement in the local newspapers and wider community locations (parks; supermarkets; town halls; community halls)?
- The study will be also be advertised using various social media platforms which may include LinkedIn, Twitter, Facebook, Instagram, Reddit, and any other relevant social media platforms identified by the research team.

Participating NHS trusts will be requested to advertise the study via their Communication team who will be provided with poster and newsletter which will direct participants to the study website. We will request that NHS trusts advertise the study as widely as possible. The study researchers will also hold online presentations and webinars to businesses to engage them and their employees/line managers. We will ask employers from across the Midlands to register interest in the trial in their commitment to support their employees/line manager. The role of the employer acts as a gatekeeper to the prospective participants, the employees and line manager, who we wish to recruit. Any employers that are interested can meet with the research team who will contact explain the study in more detail and outline the minimum commitment expected by employers (e.g., providing resources such as computer and internet, allowing employees to complete intervention related activities during normal work hours). Once an employer registers with the study, we will ask employers to advertise our study via different internal channels to their staff. Interested employees and line manager will be able to register their voluntary interest in the study by contacting the research team directly without needing to speak to their employer. The research team will contact participants (employees and line managers) with a link to consent for an online eligibility screener. The research team will then contact eligible employees and line manager by sending them a participant information sheet and asking them to complete a consent form (mirroring versions for employees of partner employers and individuals) if wishing to participate. Individuals recruited from the wider community may not have employers acting as a gatekeeper, therefore there may not agreement that they will be allowed to complete the trial “MHELW sessions” during working hours. Because this is different for individuals who have not been recruited through a partner, there will be separate mirroring PIS’s and consent forms for MENTOR.

**Consenting procedure**

There will be 3 levels of consent. Firstly, we will obtain site-level consent from the employer to host the study (implied consent will be taken if we are given access to the business). Individual-level consent will be obtained from managers involved in managing individuals with a clinical diagnosis of mental health problems and workers who agree to take part in the study. Participants will be initially asked to express an interest in taking part in the study, after which they will be invited to consent and complete the screening questionnaires and subsequently complete the eligibility screening questionnaire. There will be two mirroring versions of the expression of interest questionnaire: one for employees recruited via partner employers and one for individuals whose employer has not signed up and who have been directly approached. The expression of interest for individuals from the latter route will additionally be asked for their workplace address to ensure they are in the Midlands based workforce and to ensure our local Mind can deliver the study sessions. To ensure unintended disclosures do not occur as a result of this process, workers who are approached in this way will be explicitly made aware that their consent will mean that we approach their named line managers also for the study. We will also advertise the study in the workplace who expressed an interest in the study and provide contact details for employees/line managers to take part.

We will ensure that the identity of the employee is not revealed to the line manager until both have consented to participate. Employers will be fully briefed about the study and we would anticipate that a senior manager within the business will be allocated by the business to be our main point of contact. This may be e.g., CEO, senior manager, occupational health advisor, human resources manager, etc. We will also provide information and support which the employers will receive in preparation for the study. Prior to finalisation, the nature, content and feasibility of this input will be discussed with a number of business partners to ensure their perspectives are fully taken into account. Only if an employee and a line manager both consent to take part in the study will we proceed, as the MHELW requires study contact with both.

**Study setting**

The interventions will be conducted in the workplace and online, that is, the intervention site is the business. Working individuals who do not have partner employers acting as gatekeepers are free to decide when they participate in the study. However, non-partner employers are not obliged to allow participation during working hours, and this is made clear on the working individual consent form versions.

**Outcomes: Data collection**

The main outcome measures of the full RCT will be used. In addition to assessing the fidelity of the intervention with respect to key outcome measure scores at 3 months assessments will be completed at baseline and 3 months (at intervention end). Each participant (intervention and control group) will be involved in the study for a maximum of 3 months in total at which point primary and secondary outcome data will be collected at baseline and 3 months in both allocation arms. Participants in the control group will receive the same intervention after a 3-month delay, as part of service delivery by Mind, but no further outcome data will be collected from them. Since the line managers will have some of the study interventions, we will explore how the intervention impacted line managers mental health awareness, line management skills and job demand. All data collection of outcome measures and pre-screening scales are administered using the Qualtrics platform, with data stored on the Qualtrics servers in accordance with GDPR governance. A summary of the outcome measures at the various time points is provided in table 1.

***Feasibility and acceptability of MHELW intervention (measured at 3 months).***

**Feasibility:**

- Recruitment of 15% (n=55) employees of the full RCT sample size (n=365 with 25% attrition rate) in a 5-month recruitment period (May to end of September 2021)
- Retention rate of ≥60% as measured by attendance at the post intervention assessment
- Estimates of eligible participants recruited, failures to recruit due to recruitment issues and participants dropping out due to feasibility issues
- Completion rate of study questionnaires (employee and line manager) at baseline and 3 months for both intervention and control groups, reported as percentage missing data for each assessment schedule at baseline and 3 months.

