Data analysis will be performed after the last trial participant has completed their 3-month post-intervention. Descriptive statistics (means, SDs, and medians) will be used to report recruitment, retention rates and efficacy outcomes measures (both primary and secondary). Baseline between-group differences will be tested by conducting independent sample t-tests between the intervention group and the control on outcomes measures. A 2 x 2 ANOVA - with Time as the within-subject variable (baseline and 3-month post-intervention) and Condition (MENTOR and control condition) as the between-subject variable – will be conducted to test whether outcome measures improved in the active condition relative to the control at the 3-month post-intervention time-point. Intervention adherence will be calculated by assessing the response rate of participants receiving the intervention, response rate of completed questionnaires, and the number of sessions completed by intervention group participants. Recruitment and dropout rates will be evaluated using absolute and percentage frequencies. Analyses will be performed using statistical software Stata (Stata, version. 16.0; Stata Corp) and SPSS version 24. The intention-to-treat (ITT) principle will be applied to the primary analyses with all participants’ data being analysed as per their assigned intervention at baseline. Following randomisation participants who withdrew consent or those with a protocol violation concerning eligibility will be excluded from the ITT analysis. Participants with missing baseline information and those who do not complete intervention or are lost to follow-up will be included in the dataset; multiple data imputation and sensitivity analyses will be performed. Summary statistics will be provided for all variables.

Data will be collected using online proforma, the pre-screen questionnaire will be administered using Qualtrics survey platform. All data collection of outcome measures and pre-screening scales are administered using the Qualtrics platform, with data stored on the Qualtrics servers in accordance with GDPR governance. Any notes that the MHELW makes will be uploaded and made anonymous in the same way. MHELW will be provided access to the Qualtrics platform using a unique identification code via the email address MHELW provides with a chosen password to upload any intervention notes.

1. **Process Evaluation**

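### The 60% retention criterion is not reconciled with the 25% attrition behind the sample sizes, and meeting it does not support a full RCT of 365

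*Protocol*

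**What the plan says.** The section on the full RCT sample size derives 292 participants (146 per arm) for d = 0.33 with an "alpha error rate of 0.05 (two-tailed) and a beta error rate of 0.20". It then raises the total: "we anticipate we may need to obtain consent from up to 365 participants at randomisation, anticipating a 25% attrition rate". The feasibility sample size section sets 56 participants, 28 per arm, "factoring a 25% attrition rate as describe above for the full RCT".

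The feasibility criteria repeat the full-trial figure, "Recruitment of 15% (n=55) employees of the full RCT sample size (n=365 with 25% attrition rate", and the next bullet reads "Retention rate of ≥60% as measured by attendance at the post intervention assessment". That bullet names no arm and no denominator. A later bullet in the same list reports questionnaire completion at baseline and 3 months, as percentage missing, for both groups. The data analysis plan adds only that "Recruitment and dropout rates will be evaluated using absolute and percentage frequencies". The data collection section and Table 1 show that the 3-month outcome questionnaires are completed online through Qualtrics.

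**The concern.** The feasibility sample size section says the pilot should supply the parameters needed to judge a full RCT based on the sample size calculation. Attrition is an input to that calculation. Yet the numerical criterion for it sits 15 percentage points below the retention assumed (60% against 75%), with no stated link.

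The criterion could therefore be reported as met on data that do not support the full trial at its stated size. A reader of the pilot report could take 365 forward when the observed loss calls for appreciably more. The wording also leaves the numerator open, since nobody attends an online questionnaire, and leaves the denominator unstated.

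**Working it through.** **Inputs.** d = 0.33, two-sided alpha 0.05, power 0.80, 292 before and 365 after inflation, 25% attrition (full RCT sample size section); 56 in the pilot, 28 per arm (feasibility sample size section); 60% retention (feasibility criteria).

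**1. Reproduce the plan's figure.** Two-sample t-test, noncentral t with df = 2n − 2 and noncentrality d√(n/2). At n = 146 per arm the noncentrality is 0.33 × √73 = 2.82 and power is 80.2%. This is the smallest n reaching 80%, so 292 reproduces.

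**2. Check the inflation.** 292 × 1.25 = 365, but allowing for 25% loss means dividing: 292/0.75 = 389.3, so 390. The figure 365 equals 292/0.80, so it is sufficient only at 80% retention.

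**3. Power at different retention rates.**

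| Randomised | Retention | Analysed | Per arm | Power for d = 0.33 |
|---|---|---|---|---|
| 365 | 80% | 292 | 146 | 80.2% |
| 365 | 75% | 273.75 | 136.9 | 77.6% |
| 365 | 60% | 219 | 109.5 | 68.1% |
| 390 | 75% | 292.5 | 146.25 | 80.3% |
| 390 | 60% | 234 | 117 | 71.0% |

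The drop from the plan's own attrition to the criterion's limit is thus from about 78% to about 68%. Keeping 292 analysed at 60% retention needs 292/0.60 = 486.7, so 487 randomised. With 219 analysed, the effect detectable at 80% power is about d = 0.38.

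**4. What meeting the criterion shows.** 0.60 × 56 = 33.6, so the criterion is met at 34 of 56 (60.7%). Exact binomial probability of 34 or more:

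| True retention | 50% | 55% | 60% | 65% | 70% | 75% |
|---|---|---|---|---|---|---|
| Criterion met | 7% | 23.5% | 51% | 79% | 95% | 99.4% |

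It is usually met at a true 65%, well short of the assumed 75%, so meeting it says little about the 25% assumption.

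**5. Precision.** At 34/56 the exact 95% interval is 46.8% to 73.5%, just excluding 75%. At 35/56 (62.5%) it is 48.5% to 75.1%, which includes it.

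**6. Would a plain 75% cut-off be better?** It would mean 42 of 56. At a true 75% this is reached 57% of the time, and 21/28 in both arms only 36% of the time. A hard cut-off, above all one per arm, would often fail a trial that meets its own assumption.

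**The case against.** The strongest reply is that a minimum acceptable rate and a planning expectation are different quantities, and a floor normally lies below the expectation. As a floor, 60% behaves reasonably: it is met 99.4% of the time at a true 75% and 7% of the time at a true 50%. The protocol writes no progression rule, describes 365 as an upper figure that may be needed, and will report observed retention, which can be used to re-size the full trial. All of this stands. A reader might infer that the criterion contradicts the sizing, or that it passes the trial as feasible; the text supports neither.

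A reader might also infer that retention is judged only as a figure pooled over arms, so that heavy loss in one arm could be hidden. The protocol does not say so. It is silent on arm, and the same list reports questionnaire completion for both groups, which is close to the same quantity because the outcome measures are online questionnaires. Greater loyalty to follow-up in the waiting-list arm is also conjecture: the protocol does not make delayed treatment depend on completing the 3-month assessment.

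Nor can it be said in general that a pilot meeting the criterion rules out 75% retention. That is true at 34/56 and already fails at 35/56.

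The missing link remains. The protocol itself fixes both numbers, in adjacent bullets, and attaches no sample size consequence to retention between them.

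**Conclusion.** The point holds as an unreconciled inconsistency. The criterion can be met at up to 40% loss, where 365 randomised would give about 68% power, against about 78% at the stated 25% loss, and where 487 would be needed instead of 365. The 365 figure is itself short for 25% attrition, which needs 390.

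This rests on three assumptions: the protocol's own effect size and simple two-group comparison; power counted on participants with 3-month data; and 365 carried forward unchanged, to which nothing in the protocol commits the sponsor. Severity is moderate at most. The pilot's own conduct and validity are unaffected, and the consequence falls on a later trial that would be planned separately.

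**What to change.** - Keep 60% as the floor and state what follows. Below 60%: not feasible as designed. At 60% or more: feasible only with the full RCT re-sized as 292 divided by observed retention, which gives 390 at 75% and 487 at 60%. State that 365 is adequate only at about 80% retention or more.
- Correct the inflation in the full RCT sample size section to 390, or state that 365 corresponds to 20% loss.
- Apply the rule to overall retention, with all randomised as denominator and a 95% confidence interval. The interval shows how uncertain the re-sizing is: an observed 42/56 has a Wilson interval of 62.3% to 84.5%, or 292/0.845 = 346 to 292/0.623 = 469 randomised.
- Report retention by arm descriptively to show any differential loss, without a per-arm threshold, since 28 per arm is too few.
- Define retention as completing the 3-month online questionnaire.

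The cost is protocol wording and a few confidence intervals. The downside for the sponsor is that meeting the 60% floor would no longer by itself support the 365 figure.
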